#### Population

All study participants (both experimental and control group) are people with mental vulnerabilities. RC students will be matched with panel members based on relevant key characteristics through propensity score matching [48].

**Inclusion Criteria.** To be included in the experimental group, people need to be current RC students at the moment of recruitment (in any role, so including volunteers and employees). Moreover, participants need to experience SMI or mental vulnerabilities (both self-reported or diagnosed).

**Exclusion Criteria.** Participants are not eligible if they do not sufficiently master the Dutch language to properly understand and fill out the surveys (even with assistance from the POP group experiential researchers). Specifically for the control group, participants will be excluded from the matching procedure if they are involved in an RC or similar initiatives (i.e., recovery-oriented consumer run organisations) at time of the baseline measurement. If panel members visit one of the included RCs at the time of recruitment, they will be allocated to the experimental group.

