#### Procedures

**Recruitment.** The recruitment of participants in this study is two-fold. First and most importantly, participants for the experimental group will be recruited from four RCs in the Netherlands. Enik is the base site of this research project, and we additionally include three other RCs for two reasons: (1) to increase the generalizability and quality of our data and (2) to reach a sample size that is sufficiently large to draw conclusions with a satisfactory certainty. The three additional RCs were selected in collaboration with the co-founder of Enik, and were considered to be well-established and based on a similar philosophy.

RC students will be invited via physical (i.e., posters, flyers) and digital promotion material (i.e., email, newsletter, information page on the RC website, video). Furthermore, facilitators of RC workshops will recruit participants in their groups, and the research team (incl. POP group) will actively recruit participants in the RC’s social meeting place and team meetings. In addition, online and physical information sessions will be hosted to provide information about participation, and assistance with enrolling. When willing to participate, participants receive a digital information letter, provide informed consent and fill out an online application form. Members from the POP group can assist participants in this process if necessary.

Second, as part of regular maintenance of the panel, recruitment for the panel is done via physical and digital promotion materials, which will be distributed among the target population in mental health services’ divisions for people with SMI, and in public (e.g., online advertisements or advertisements in newsletters).

**Between-Group Differences.** RC students are considered similar to the panel’s target population in many ways (e.g., SMI, use of care), yet the most important between-group difference is that those in the experimental group are (or have recently been) actively involved with one of the participating RCs, while members of the panel that are included as controls are not.

**Matching.** To control for potential confounding given the natural (non-randomized) assignment of conditions, we will use propensity score matching and/or exact matching. All participants who have completed at least two waves will be considered for the matching procedure.

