Variables that will be used for the matching are gender, age, nationality, level of education and diagnoses (psychotic disorders, mood disorders, anxiety disorders, personality disorders, substance use disorders, neurodevelopmental disorders, eating disorders). If someone does not have an official diagnosis, we will use self-reported diagnosis as a proxy. Although potentially relevant, duration of service use will not be used as matching variable since true baseline data are unavailable; the experimental group may be already active at the RC for a significant amount of time at t_0,_ which may have impacted service use. Each participant from the experimental group will be matched to one or more participants from the control group. Given the large sample size of the control group and the limited number of matching variables, we will likely retrieve multiple good matches per RC partaker, reducing uncertainties and increasing reliability.

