#### Variables of interest study 1A and 1B

For clarity, the variables of interest are reported here for the effectiveness study (1A) and the economic evaluation (1B) separately. Demographic and descriptive variables are relevant for both studies 1A and 1B.

**Demographic and Descriptive Variables.** Basic demographics (gender, age, nationality, level of education, employment status, housing), and SMI-specific variables (mental health problems; self-reported and officially diagnosed, duration of mental health problems, health care use) will be used to describe the sample. As noted, many of these variables will be used to match participants from the control group (panel members) with participants from the experimental group (RC students). Furthermore, participants in the experimental group will indicate in what way and how frequently they are active at the RC.

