#### Variables of interest study 1B: economic evaluation

***Resource Use.*** To assess (informal) care use of participants, the Trimbos and iMTA questionnaire on Costs associated with Psychiatric illness (TiC-P; [58]) will be used, with a recall period of three months. This includes questions on medication and contact-hours with care providers but also questions about informal care received from one’s own social network (e.g., family, acquaintances, neighbours). To assess community outcomes such as employment, again the TiC-P [58] will be used. This includes questions on whether participants have employment or are active as volunteer, absenteeism and presenteeism of their (un)paid jobs. The recall period for absenteeism and presenteeism is four weeks. Housing status (e.g., living independently, living in a hospital/sheltered or supported housing residence, having no permanent residence) will also be determined by one item that we formulated (not in the TiC-P).

***Quality-Adjusted Life Years.*** In line with the Dutch guidelines for economic evaluations, quality-adjusted life years (i.e., QALYs) will be computed using utilities derived from the EuroQol-5-dimensions-5-level-questionaire (EQ-5D-5 L; [59]). The EQ-5D-5 L consists of six items, of which five inquire about specific restrictions in daily life (i.e., health states), with regards to mobility, self-care, usual activities, pain/discomfort and anxiety/depression. Possible answers on these items range from 1 to 5, where ‘1’ = Indicating no problem and ‘5’ = Indicating unable to/extreme problems. One final item regards the general health state (the EQ VAS: “We would like to know how good or bad your health is TODAY. Mark an X on the scale to indicate how your health is TODAY”). This general health state is represented by a number between 0 and 100, where ‘0’ = The worst health you can imagine, and ‘100’ = The best health you can imagine. The health states from the EQ-5D-5 L will be computed into utilities using the Dutch tariffs of EuroQol [60]. By means of the area under the curve method, time periods between assessment waves will be weighted by these utilities, which results in QALYs adjusted over the timeframe of 24 months. An overview of all measures can be found in Table 1.

**Table 1 Tab1:** Overview of all variables of interest and its matching instruments as used in Study 1

Measurement level	Variable of interest	Instrument	Reference
Primary	Empowerment	NEL	Boevink, Kroon (49)

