#### Analysis study 1A: effectiveness

To determine the effectiveness of RC attendance we will conduct multi-level regression analyses with three levels: (1) repeated observations (2) within participants and (3) participants in pairs of intervention and propensity score matched controls. While participants in the experimental group can be considered to occupy multiple sites (i.e. a multisite study), participants from the control group strictly seen cannot. Hence, through likelihood ratio testing it will be determined whether including an additional fourth level (random intercept) for site leads to a significant better model fit, in which all participants in the control group will be considered to reside at a single unique site. As no true pre-intervention randomization is possible, the effect analyses will be performed slightly modified to as what is recommended by Twisk, Bosman [66] in that the fixed effect for group will be included in the repeated measures models, alongside the fixed effect for time and the interaction between those. In addition, the models will be fitted without intercept, aiding in interpretation of potential (not intervention related) differences between the control and experimental group. All multi-level analyses will be performed using the R packages lme4 [67] and lmerTest [68].

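### The group-by-time effect measures change after t0 among people already attending an RC, so it leaves out any benefit gained before t0, and the plan describes the remaining group difference as unrelated to the intervention

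*Protocol article*

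**What the plan says.** All references are to the protocol article, Study 1.

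- **Population, inclusion criteria.** For the experimental group, "people need to be current RC students at the moment of recruitment". Any role counts, volunteers and employees included. No limit is set on time since first attendance.
- **Procedures, Matching.** Duration of service use is not a matching variable because "true baseline data are unavailable; the experimental group may be already active at the RC for a significant amount of time at" t0, and this may already have affected service use.
- **Variables of interest study 1A and 1B.** On RC exposure, "participants in the experimental group will indicate in what way and how frequently they are active at the RC".
- **Analyses.** Baseline differences left over after matching will be checked and, where judged necessary, adjusted for. The two sensitivity analyses named for RC exposure concern cross-overs and course attendance.
- **Analysis study 1A.** Because there was no randomisation before the intervention, "the fixed effect for group will be included in the repeated measures models, alongside the fixed effect for time and the interaction between those". The models have no intercept, a choice described as "aiding in interpretation of potential (not intervention related) differences between the control and experimental group".
- **Analysis study 1B.** A responder is defined by reliable change on the NEL between t0 and t4.
- **Research questions.** RQ 1 asks whether, and how much, attending an RC affects empowerment in the long term.

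**The concern.** The plan accepts that t0 is not a pre-exposure measurement for the RC group, but uses this only to drop one matching variable. The effect model then treats t0 as the reference point and describes the group difference as having nothing to do with the intervention. If attendance before t0 has already raised empowerment, that gain sits in the group difference and not in the interaction. Adjusting for baseline differences could remove it as well.

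Established attenders who have little left to gain would pull the interaction towards zero. A null interaction could then be taken to mean that RCs do nothing, when it shows only that existing attenders did not improve more than controls after an arbitrary date. The cost-effectiveness ratio built on responders carries the same risk.

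**Working it through.** **Step 1: where a benefit gained before t0 goes.** Take t0 as the time reference. The expected mean is

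E[Y] = time(t) + β·G + γ(t)·G, with γ(t0) = 0.

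At t0 the difference between groups is β. Leaving out the intercept only re-expresses this: the model reports a t0 mean for each group, and β is their difference. The interaction is unchanged.

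Let the total benefit be B, with a share p present at t0 and the rest reached by t2 and kept. Then β = pB (plus any selection difference) and γ = (1 − p)B. With B = 0.3 and no selection difference:

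| p | group difference at t0 | interaction at t2 and t4 |
|---|---|---|
| 0 | 0 | 0.300 |
| 0.25 | 0.075 | 0.225 |
| 0.50 | 0.150 | 0.150 |
| 0.75 | 0.225 | 0.075 |
| 1 | 0.300 | 0 |

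**Step 2: can tenure be long?** The base-site RC opened in 2015 (Co-research as methodology), and costs are indexed to a 2022 start (Analysis study 1B). Up to 2022 − 2015 = 7 years is therefore possible at that site. The other three RCs were chosen as well established. The documents give no distribution of tenure, so p is unknown.

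**Step 3: the plan's own power figure.** Inputs from Sample size: 125 per group, d = 0.3, correlation 0.6 between subsequent measurements, 30% dropout at t4, power 82.8%. Assumed here: two-sided alpha 0.05, waves t0, t2 and t4, retention 100/85/70%, generalised least squares with a normal approximation.

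Power = Φ(δ/SE − 1.96) + Φ(−δ/SE − 1.96).

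The 82.8% is reproduced with correlation falling with lag (0.6, then 0.36), equal group means at t0, and one effect common to t2 and t4. SE = 0.1032; 0.3/0.1032 = 2.907; 2.907 − 1.96 = 0.947; Φ = 0.828. This match is not unique, since the article does not state the simulated model, and the set-up has no free group term.

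**Step 4: the same inputs with the group term that the analysis section includes.**

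| Correlation 0.6 | Effect tested | SE | Power, δ = 0.30 | Power, δ = 0.15 |
|---|---|---|---|---|
| falling with lag | t4 alone | 0.1597 | 46.7% | 15.6% |
| equal at all lags | t4 alone | 0.1297 | 63.8% | 21.2% |
| falling with lag | t2 and t4 together | 0.1183 | 71.8% | 24.5% |
| equal at all lags | t2 and t4 together | 0.1064 | 80.5% | 29.1% |

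Example for the last row: 0.15/0.1064 = 1.41; 1.41 − 1.96 = −0.55; Φ = 0.291. The second term is negligible.

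With p = 0.5, power is therefore about 16% to 29%. These figures illustrate the mechanism and do not estimate this study's power.

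**The case against.** The design is open about what it does. It is pragmatic, follows current attenders, and admits that t0 is not a true baseline. Benefit still accruing after t0 is captured. The t0 gap may also contain real selection differences, so keeping it out of the effect estimate is partly right. The analysis section mentions neither a t0 gap nor the interaction as the effect, and its parenthesis could be read as covering only such differences as are not due to the intervention. That reading is possible, but the text gives no means of telling the two kinds of difference apart. Once group differences are set aside, the interaction is the only term left to carry the effect.

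A reader might infer more than the documents support:

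- *That the Matching text says the opposite of the analysis section.* It speaks of service use, not empowerment. The extension to empowerment is reasonable, but it is an inference.
- *That start dates are not collected.* The article says "An overview of all measures can be found in Table 1", but that table lists only outcome and economic instruments. It also omits age, diagnosis and RC role, which the plan does use or collect. In a condensed article, silence here proves little.
- *That the exposure rules conflict and a recent ex-student could fall in either arm.* The statement that RC participants "are (or have recently been) actively involved with one of the participating RCs" describes the group. The inclusion criterion governs eligibility and requires current attendance. Past attenders among controls remain possible, since controls are excluded only for involvement in an RC or similar initiative at baseline, but nothing shows how many there are.
- *That the study has the low power shown above.* The plan sets 0.3 as the expected difference in this study, after considering how mixed RC attendance is. It does not say that 0.3 is the total benefit since first attendance, so multiplying by (1 − p) may discount twice.

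**Conclusion.** The point holds as a mismatch between the question and the estimate, together with a misleading label. As written, the primary model estimates the effect of continued attendance from t0 among existing attenders. It does not fully answer RQ 1, and the t0-to-t4 responder outcome is limited in the same way. This follows from the model's structure and the plan's own concession about t0. It rests on reading the interaction as the effect and t0 as the time reference.

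The size cannot be determined. The proportional loss p depends on tenure and on how early benefit arises, and the documents give neither. Nor can the t0 gap be credited wholly to RC attendance, because without start dates selection and earlier benefit cannot be separated.

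**What to change.** 1. In Analysis study 1A, delete the parenthesis that calls group differences unrelated to the intervention. Say instead that the t0 gap may reflect selection, earlier RC benefit, or both. Apply the same caution to adjustment for baseline differences in Analyses.
2. State that the main contrast is change after t0 among current attenders, for the NEL model and the responder outcome alike, and that a null result will not be read as no effect of RCs.
3. Obtain each student's RC start date if it is not already recorded: by a survey item if a wave remains, otherwise from RC enrolment records if these are kept. The documents do not show whether a wave is still to come.
4. Pre-specify group-by-time by tenure, with a contrast in recent starters as a supporting analysis.
5. Where panel members' past RC attendance can be obtained, add a sensitivity analysis without past attenders among the controls.

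The cost is some rewording, one or two data items and modest analysis; enrolment does not change. The downside is that the recent-starter analysis uses only part of the 125 students and will be imprecise, and the headline claim becomes narrower.

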#### Sample size

The required sample size to reach at least 80% power is determined through simulation using the R packages simstudy [61] and faux [62]. To our knowledge, no previous studies included empowerment as primary outcome variable, so our estimation of the expected effect size of Cohen’s D is based on previous work on peer support effectiveness [63] and on RC effectiveness [20]. These effect sizes were small. In our case, the hybrid nature of RC attendance and the selection of NEL subscales may potentially lower the capability to detect clinically relevant changes^5^. On the other hand, the NEL has proven to be sensitive to change in recovery-oriented practices (e.g., medium effect size in Tjaden, Mulder [64] after 18 months). All this considered, we assume an effect size of Cohen’s D = 0.3. Assuming Cohen’s D = 0.3, a Pearson’s correlation coefficient of 0.6 between subsequent measurements [64] and 30% dropout at t_4_ we expect to detect a significant difference in 82.8% of the time between the control and experimental group when a total 250 participants are to be included. Participants for the control group will be recruited from the existing panel through propensity score matching, hence the study is appropriately powered when 125 participants for the experimental group have been included and matched to 125 control participants.

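### Matching to one or more controls feeds a model of pairs with no stated matching weights; if set sizes vary, the group-by-time effect can keep part of the confounding that matching removed

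*Protocol article*

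**What the plan says.** The protocol article describes the matched structure in three places.

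- **Study 1, Procedures, Matching.** The method is left open: "we will use propensity score matching and/or exact matching". On the ratio, "Each participant from the experimental group will be matched to one or more participants from the control group", with the expectation that "we will likely retrieve multiple good matches per RC partaker, reducing uncertainties and increasing reliability". Eligibility is stated as "All participants who have completed at least two waves will be considered for the matching procedure". No maximum number of controls, caliper or replacement rule is given.
- **Sample size.** "the study is appropriately powered when 125 participants for the experimental group have been included and matched to 125 control participants".
- **Analysis study 1A: effectiveness.** The three levels are repeated observations, participants, and "participants in pairs of intervention and propensity score matched controls". On the fixed part, "the fixed effect for group will be included in the repeated measures models, alongside the fixed effect for time and the interaction between those". The R packages are named. No matching weights are mentioned.

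The Analyses section adds that baseline group differences which the matching did not account for will be checked and, where needed, controlled for.

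**The concern.** Matching one student to several controls balances the groups within each set. That balance carries over to the whole comparison only if each set contributes to the control arm in the same proportion as to the RC arm. With a constant ratio this is automatic. With a varying ratio and one count per control it is not: profiles that are common in the panel attract many controls and weigh more among controls than among RC students.

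It is natural to expect the matched-set level to repair this. For differences in level it helps in part. For change over time, which is what the group-by-time interaction estimates, a set intercept is constant over waves and drops out of each person's change. What is at stake is that the main contrast may compare groups with somewhat different case-mix, although the matching was done to avoid that.

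**Working it through.** **The plan's own figure.** The article states 82.8% power for 125 + 125 participants, with D = 0.3, correlation 0.6 and 30% dropout at t4. A generalised least squares calculation gives 82.8% under these further assumptions: waves t0, t2 and t4; correlation decaying as 0.6 per step; 15% lost before t2 and a further 15% before t4; two-sided 5%; equal baseline means; and a constant effect of 0.3 SD at t2 and t4. Other readings of the same inputs give other values, so this shows only that the figure can be reached with 1:1 matching. It does not bear on the bias.

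**Bias in the change contrast.** The inputs are assumed; the documents give none of them.

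- Half of the RC students are of type A with 5 controls each, and half of type B with 1 control each.
- Natural change from t0 to t4 differs by 0.2 SD between the types.

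Share of type A among RC students: 0.5. Share among controls when each counts once: 5 / (5 + 1) = 0.833.

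Bias = (0.833 − 0.5) × 0.2 = 0.067 SD. Relative to D = 0.3: 0.067 / 0.3 = 22%.

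With 3 against 1: 3 / (3 + 1) = 0.75, and (0.75 − 0.5) × 0.2 = 0.05 SD, or 17% of D. The direction depends on which type improves more.

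**Does the set intercept help?** The expected estimate from the article's model with complete data (group, time, interaction, person and set intercepts) has a bias in change of 0.067 SD whether the set variance is close to 0, 0.1 or 0.3 of the total. It is the same because the set intercept cancels from within-person change.

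**When the bias is zero.** If the matching variables shift the level of empowerment but not its change, the same calculation gives a bias in change of 0.

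**A second illustration.** Take one continuous matching variable, with 5, 3 and 1 controls across its thirds.

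| Effect of the variable (per SD) | Bias at t4, sets ignored | Bias at t4, set intercept | Bias in change, either way |
|---|---|---|---|
| Level 0.3, change 0 | 0.150 | 0.107 | 0 |
| Level 0.5, change 0 | 0.244 | 0.109 | 0 |
| Level 0.3, change 0.1 | 0.196 | 0.148 | 0.049 |
| Level 0.3, change 0.2 | 0.243 | 0.188 | 0.097 |

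The set level reduces the bias in level and leaves the bias in change untouched.

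**What weighting does to balance.** In simulated variable-ratio matching (up to 5 controls, caliper 0.1 SD, raw standardised difference 0.3 to 1.0, pool of 400 to 1,400), counting each control once left a standardised difference of 0.04 to 0.41. Weighting each control by 1/k, where k is the number of controls in its set, left 0.003 or less.

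**What weighting costs in precision.** In the 5-and-1 example with 125 students, and ignoring correlation within sets, the variance of the group difference is proportional to:

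- 1:1: 1/125 + 1/125 = 0.0160
- weighted: mean of 1/k = (1/5 + 1)/2 = 0.6, so 1/125 + 0.6/125 = 0.0128
- unweighted: mean of 3 controls gives 375, so 1/125 + 1/375 = 0.0107

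The standard error under weighting is √(0.0128/0.0107) ≈ 1.10 times the unweighted one, and √(0.0128/0.0160) = 0.89 times that of 1:1.

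**The case against.** **The article nowhere says that the analysis is unweighted.** It is condensed, and weights, caliper and maximum ratio may stand in an analysis plan that is not shown. The ratio could also be fixed for everyone once the pool is known. This stands, and it makes the point conditional on a varying ratio and on fitting the model as written. It does not remove the point, because the article does specify the model's levels, fixed effects and software, and it describes pairs where its own matching rule expects larger sets.

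**The check on baseline differences may catch the problem.** That safeguard covers differences that the matching did not account for. Imbalance in the matching variables recreated by unequal set sizes falls outside that wording, and adjusting for a main effect would leave a difference in change largely in place.

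**The magnitude is constructed.** This is correct. The set sizes and the 0.2 SD are assumptions, and the bias is zero if the matching variables do not predict change.

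**Stronger readings.** A reader might infer that easily matched students dominate the control arm and that the matching is undone. The calculations do not support that: the residual difference ranged down to 0.04, and level differences are partly absorbed by the set intercept. A reader might also infer that planning "125 participants for the experimental group have been included and matched to 125 control participants" wastes the panel. The Sample size section reads as a sufficient minimum, and the Matching paragraph already intends several controls where they exist. Finally, a reader might conclude that a fixed 1:3 ratio is the cure. The number of eligible controls is not stated, so 375 good matches cannot be assumed. Forcing a third match can worsen balance, and a caliper can drop hard-to-match students. Equating variances, (4/3)/n = 2/125 gives n = 83.3, so with fewer than 84 students retained, 1:3 has less power than 1:1.

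**Conclusion.** The point holds in conditional form. The matching rule and the analysis model do not describe the same structure. If the number of controls varies between students and the model is fitted as described, the group-by-time estimate loses some of the balance that matching gained, to the extent that the matching variables predict change in empowerment.

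Under the assumed inputs the bias is 0.05 to 0.10 SD, with 0.067 SD (22% of D = 0.3) in the simplest example, and zero if those variables affect level only. Different two-year courses across the diagnostic groups used for matching are plausible, but the documents give no figure for this. The finding calls for a correction of the analysis description. It does not show that the design fails or that the planned sample is inadequate.

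**What to change.** 1. In Analysis study 1A, replace pairs with matched sets, so that the model agrees with the Matching paragraph.
2. Where the ratio varies, weight each RC student by 1 and each control by 1/(number of controls in the set), in both the effectiveness and the economic analyses.
3. Check and report balance in the weighted sample, since that is the comparison being analysed.
4. In Sample size, describe 125:125 as the minimum, with further controls adding precision.
5. State how the weights enter the mixed model. If they enter as residual-variance weights, they reproduce the 1/k weighting for change with complete data, but not for differences in level, and the model-based standard errors should not be relied on. Resampling whole matched sets within the bootstrapping already planned would deal with the standard errors.

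The cost is a change of wording and a small amount of programming; no additional participants are needed. In the 5-and-1 example, weighting makes the standard error about 10% larger than the unweighted analysis and about 11% smaller than 1:1 matching. If the sponsor prefers one constant ratio, weights are not needed, but the ratio should be stated in all three places.
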